## 7.0 TOXICITY MANAGEMENT

### 7.1 Reactions Thought Definitely, Possibly, or Probably Related to Study Vaccine

#### 7.1.1 Local reactions

Local reactions will be graded using the local reaction assessment scale (Table 1).

Table 1: Local reaction assessment

| Grade                           | Description                                                                                             |
|---------------------------------|---------------------------------------------------------------------------------------------------------|
| 0 = None                        | N/A                                                                                                     |
| 1 = Mild                        | Macular or papular eruption, erythema or induration that is asymptomatic or mildly symptomatic          |
| 2 = Moderate                    | Macular or papular eruption, erythema or induration with pruritus or other associated moderate symptoms |
| 3= Severe                       | Ulceration, blistering, superinfection or phlebitis                                                     |
| 4= Potentially Life-threatening | Necrosis of the skin                                                                                    |

#### 7.1.2 Systemic reactions

Systemic reactions will be graded according to the Division of AIDS Table for Grading Adult Adverse Experiences (see Appendix IV). The Principal Investigator should be contacted within 48 hours for any non-local Grade 3 or 4 reactions (for example, elevated temperatures following immunization) thought definitely, possibly, or probably related to vaccination with LC002.

### 7.2 Antiretroviral Drugs

Unanticipated and anticipated toxicities from the HAART regimen will be graded according to the Division of AIDS Table for Grading Adult Adverse Experiences (see Appendix IV). Any Grade 3 or 4 toxicities that result in a temporary or permanent change in an antiretroviral therapy must be reported to the Principal Investigator.

Anticipated toxicities resulting from components of the HAART regimen will be managed by the subject's clinician according to best clinical practice including dose reductions when indicated.

If the HIV-1 viral load becomes detectable (plasma HIV-1 RNA > 1,000 copies/mL) either during the treatment phase (Day 0 to 28) or 48-week follow up, it should be repeated one week later and compliance issues should be ruled out. If the repeated HIV-1 viral load is detectable (plasma HIV-1 RNA > 1,000 copies/ml) genotyping should be performed and HAART changed if necessary.

In case of virologic failure, genotyping will also be performed on the nef gene. As the nef gene contained in the DNA of LC002 is truncated, detection of a truncated nef gene would indicate recombination of the patient's virus with the vaccine. All patients with virologic failure will be followed for the complete 48-week follow up period.

## 8.0 CRITERIA FOR TREATMENT DISCONTINUATION

- Vaccine-related toxicity (see section 7.0 Toxicity Management).
- Requirement of prohibited concomitant medications (see section 5.4)
- Failure by the subject to attend 2 consecutive clinic visits.
- Pregnancy or breast-feeding.
- Request by the subject to withdraw.
- Request of the primary care provider if s/he thinks the study is no longer in the best interest of the subject.
- Subject judged by the investigator to be at significant risk of failing to comply with the provisions of the protocol as to cause harm to self or seriously interfere with the validity of the study results.
- At the discretion of the investigator or sponsor.

## 9.0 STATISTICAL CONSIDERATIONS

### 9.1 General Design Issues

GIHU004 is a phase I sequential dose escalation cohort study designed to select a tolerable dosing regimen for the DermaVir vaccine and to explore its immunogenicity in the study population. Three cohorts of 9 subjects each will be sequentially enrolled (depending on safety outcomes, which determine whether to dose escalate or not).

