## SCHEMA

### A PHASE I STUDY TO EVALUATE THE TOLERABILITY AND SAFETY OF A LC002, A DERMAVIR VACCINE, IN HIV-1-INFECTED SUBJECTS CURRENTLY UNDER TREATMENT WITH HIGHLY ACTIVE ANTIRETROVIRAL THERAPY (HAART)

#### DESIGN:

GIHU004, a phase I sequential dose escalation cohort study is designed to evaluate the safety and immunogenicity of three dosing regimens of LC002 for the treatment of individuals with chronic HIV-1 infection who have highly active antiretroviral therapy (HAART)-induced durable suppression of viral replication. Subjects will be assigned to one of three cohorts. Subjects in cohort 1 will be randomized to receive one low-dose LC002 vaccination (3 subjects). Further enrollment of subjects into the medium dose cohort 2 (3 subjects) and high dose cohort 3 (3 subjects) will begin only after the safety data for cohort 1 and 2, respectively, are available, and the criteria for enrolling the next cohort are met. The main criterion to advance to the next cohort will be the absence of a dose-limiting toxicity.

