#### DURATION:

Subjects will be on study for a total of 4 weeks followed by an additional 48 weeks for safety evaluations.

SAMPLE SIZE: 9 subjects (3 subjects/cohort)

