## 2.2 Rationale

### Hypothesis

Vaccination with DermaVir is safe and a dosing regimen for future clinical trials will be selected.

Treatment with HAART induces a significant rise in CD4+ cell counts that continues, at a slower rate, even several years after the initiation of a fully suppressive, continuous regimen (38). Although partial, the magnitude of HAART-induced immune restoration is sufficient to allow the safe discontinuation of antimicrobial prophylaxis against common opportunistic infections (39, 40). In contrast, HIV-specific CTL immune responses do not seem to be effectively restored by continuous HAART outside the acute infection period (14,41), and in fact tend to decline with time among subjects on HAART (42-44). For these reasons, the design of interventions aimed at restoring HIV-specific cellular immune responses are an obviously desirable addition to the current therapeutic armamentarium for the treatment of HIV infection. Several approaches have been investigated with this goal, most of which have attempted to enhance the host immune response via immunization with HIV antigens (45-50). Although some of these agents have been shown to stimulate immunogen-specific immunity, as evidenced by enhanced lymphoproliferative responses (LPRs) primarily

in subjects with high CD4+ T-cell counts, there has been no evidence of beneficial effect in terms of disease progression or alteration in plasma viral load (45-48, 51, 52). Clinical trials of various gp120 vaccines both in subjects with early HIV infection (ACTG 214) and subjects with later stage HIV infection (ACTG 209) have failed to show any effect on disease progression as measured by HIV-1 viral load or rate of decline of CD4+ cells, despite demonstration of immunologic response to vaccination (53). Similarly, a large multicenter trial (54) with the gp120 depleted inactivated Remune® product failed to show a clinical benefit of the vaccine, but humoral and cell-mediated HIV-specific immunity was demonstrated in smaller cohorts of subjects.

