### 3.0 STUDY DESIGN

This phase I trial is designed to evaluate the safety and immunogenicity of LC002 for the treatment of individuals with chronic HIV-1 infection and HAART-induced durable suppression of viral replication. The study population will include HIV-infected men and women 18 to 50 years of age with a peak plasma HIV-1 RNA > 1000 copies/mL before initiation of HAART. Eligible subjects must have been and remain on a stable HAART regimen (containing drugs of at least two different classes) without changes or interruptions within the 24 weeks prior to study entry and must have a plasma HIV-1 RNA level < 50 copies/mL at least twice within 12 weeks prior to study entry. Subjects should have a CD4+ cell count > 300 cells/mm^3 at the time of entry and a nadir CD4+ cell count > 250 cells/mm^3.

Subjects in cohort 1 will be enrolled to receive one low-dose DermaVir vaccinations (3 subjects). Further enrollment of subjects into the medium and high dose cohorts 2 and 3 (3 subjects, respectively) will begin only after the safety data for cohorts 1 and 2, respectively, are available, and the criteria for enrolling into the next cohort are met (see section 9.1.3). The main criterion to start enrolling the next dose cohort will be the absence of a dose-limiting toxicity in any of the DermaVir subjects in the prior cohort. The actual immunization will be administered once, and after the four-week treatment phase and evaluations, subjects will be followed for an additional 48 weeks for safety.

Subjects will be sequentially enrolled into each cohort:

- Cohort 1:
  - Three subjects will receive a single low-dose vaccination (0.1 mg DNA/subject, 0.8 mL total, administered over two skin sites of 80 cm^2 each, 0.4 mL/site) at study day 0.
- Cohort 2:
  - Three subjects will receive a medium-dose vaccination (0.4 mg DNA/subject, 3.2 mL total, administered over four skin sites of 80 cm^2 each, 0.8 mL/site) at study day 0
- Cohort 3:
  - Three subjects will receive a high-dose vaccination (0.8 mg DNA/subject, 6.4 mL total, administered over eight skin sites of 80 cm^2 each, 0.8 mL/site) at study day 0.

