#### 4.3 Study Enrollment Procedures

4.3.1 Prior to implementation of this protocol, the protocol and consent form must be approved by the local institutional ethics committee.

Once a candidate for study entry has been identified, details will be carefully discussed with the subject. The subject (or parent or legal guardian if the subject is under guardianship) will be asked to read and sign the consent form.

Only subjects who meet the eligibility criteria at both the screening and pre-entry visits will be enrolled. Cohorts will enroll serially. After all 3 subjects of a given cohort (#1 or #2) have received their study vaccine administrations, and have remained on study through at least the 14th day, if no subject in any cohort has experienced a Primary Safety endpoint (defined in section 9.2.1), then the study will dose escalate by opening enrollment of subjects into the next cohort.

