## 5.0 STUDY TREATMENT

### 5.1 Regimens, Administration, and Duration

Study treatment is DermaVir.

5.1.1 Subjects who meet the inclusion criteria will be sequentially enrolled into each cohort:

- Cohort 1:
  - Three subjects will receive a single low-dose vaccination (0.1 mg DNA/subject, 0.8 mL total, administered over two skin sites of 80 cm^2 each, 0.4 mL/site) at study day 0.
- Cohort 2:
  - Three subjects will receive a medium-dose vaccination (0.4 mg DNA/subject, 3.2 mL total, administered over four skin sites of 80 cm^2 each, 0.8 mL/site) at study day 0.
- Cohort 3:
  - Three subjects will receive a high-dose vaccination (0.8 mg DNA/subject, 6.4 mL total, administered over eight skin sites of 80 cm^2 each, 0.8 mL/site) at study day 0.

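### Section 9.1 plans three cohorts of 9 subjects (27 in all), while every other statement of size in the protocol gives 3 per cohort (9 in all)

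*Protocol*

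**What the plan says.** Section 9.1 (General Design Issues) describes a sequential dose-escalation study and sets its size: "Three cohorts of 9 subjects each will be sequentially enrolled", subject to safety outcomes.

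The rest of the protocol gives a different size:

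- **Schema, Sample Size line:** "SAMPLE SIZE: 9 subjects (3 subjects/cohort"). This is the only line labelled as sample size and the only place where the total of 9 is written out.
- **Schema, Design:** "Further enrollment of subjects into the medium dose cohort 2 (3 subjects) and high dose cohort 3 (3 subjects) will begin only after" the earlier cohort's safety data are available. Cohort 1 is also given as 3 subjects there.
- **Section 3.0:** "Subjects in cohort 1 will be enrolled to receive one low-dose DermaVir vaccinations (3 subjects"), with 3 each for cohorts 2 and 3.
- **Section 4.3:** the escalation step is written for cohorts 1 and 2 and starts "After all 3 subjects of a given cohort (#1 or #2) have received their study vaccine administrations".
- **Section 5.1.1 and the Schema regimen list:** three subjects in each of the three cohorts, for example "Three subjects will receive a high-dose vaccination (0.8 mg DNA/subject, 6.4 mL total".

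Section 9.1.3 allows escalation only if no subject in the current or a lower cohort has had a primary safety endpoint, and it asks for at least two subjects followed for 14 days. Section 9.3 caps replacements at two per cohort.

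**The concern.** The statistics section and the rest of the protocol disagree threefold on how many people will receive an experimental DNA vaccine. Section 9.1 contains the only cohort size given in Section 9, so a reader who takes the design from there will expect 27 vaccinated subjects. A reader who takes it from the Schema will expect 9.

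Two things depend on the figure. One is the human exposure that the protocol asks to have approved. The other is how the escalation rule behaves. A rule that requires zero events is much stricter when applied to 9 subjects than to 3, and a clean cohort of 9 carries more information than a clean cohort of 3.

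**Working it through.** **Inputs from the protocol.** Number of cohorts: 3. Subjects per cohort: 9 (Section 9.1) or 3 (Schema, Sections 3.0, 4.3 and 5.1.1). Stated total: 9 (Schema). Replacement cap: 2 per cohort (Section 9.3). Escalation condition: zero primary safety endpoints (Section 9.1.3). The protocol gives no confidence level, power, target precision or assumed event rate.

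**Step 1. Reproduce the stated total.**

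- With Section 9.1: 3 × 9 = 27. This does not match the Schema's 9.
- With the other sections: 3 × 3 = 9. This matches exactly.

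**Step 2. Can replacements explain the gap?**

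- Cohorts of 3: at most 3 × (3 + 2) = 15 enrolled.
- Cohorts of 9: at most 3 × (9 + 2) = 33 enrolled.

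The ceiling of 15 is still well below 27, so no reading of Section 9.3 reconciles the two.

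**Step 3. Effect on the zero-event escalation rule (illustrative).** The true rates p are assumptions. The calculation also assumes independent subjects, the same rate in cohorts 1 and 2, full cohorts, and all events known at the decision.

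Chance of at least one endpoint in a cohort of n: 1 − (1 − p)^n. Chance of passing both escalation steps: (1 − p)^(2n), so the exponent is 6 for n = 3 and 18 for n = 9.

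| Assumed p | At least one event, n = 3 | At least one event, n = 9 | Both steps passed, n = 3 | Both steps passed, n = 9 |
|---|---|---|---|---|
| 10% | 27.1% | 61.3% | 53.1% | 15.0% |
| 20% | 48.8% | 86.6% | 26.2% | 1.8% |

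**Step 4. Meaning of a clean cohort (illustrative).** The exact one-sided 95% upper bound after zero events is 1 − 0.05^(1/n).

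- n = 3: 1 − 0.05^(1/3) = 63.2%.
- n = 9: 1 − 0.05^(1/9) = 28.3%.

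With two-sided 95% limits, 1 − 0.025^(1/n), the values are 70.8% and 33.6%. The level and the sidedness are assumptions made here.

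**The case against.** The strongest reply is that nobody running the trial would be misled. Every passage that governs enrolment and dosing uses 3 per cohort. The requirement in Section 9.1.3 for at least two followed subjects also fits a cohort of 3 better than a cohort of 9. The likeliest explanation is that the overall total of 9 was written where the cohort size belonged, and nothing else in the protocol is built on 27. All of this stands. It shows which figure to keep, but it does not justify leaving a threefold conflict over human exposure in the protocol.

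Two stronger readings are tempting, and the document supports neither.

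- **That the achievable safety precision is misstated.** Section 9 sets no confidence level, interval width, detectable rate or power, so no stated precision can be wrong. The bounds above only illustrate what depends on the cohort size. Pooling across cohorts to obtain bounds for 9 or 27 subjects would further assume one event rate over doses from 0.1 to 0.8 mg, an eightfold range.
- **That the protocol plans to conclude safety from 3 subjects per dose.** Section 2.2 does say "Vaccination with DermaVir is safe and a dosing regimen for future clinical trials will be selected", but it does so as a hypothesis within the rationale. The primary objective in Section 1.1 is to evaluate safety, and escalation on the absence of events does not claim a statistical comparison between doses. Whether exact limits accompany the event counts is reporting detail commonly left to the statistical analysis plan.

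**Conclusion.** The contradiction is real and lies in current text. Section 9.1 implies 27 subjects, while the Schema states 9 and every other statement of cohort size gives 3. The difference is threefold and replacements do not account for it. The weight of the document is on 3 per cohort, so the sentence in Section 9.1 is the one to correct. This conclusion rests on counting alone and needs no statistical assumption.

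The consequences for the escalation rule and for a clean cohort (about 63% against about 28% as the excluded event rate) do rest on assumptions: a one-sided 95% level for the bounds, and the assumed rates for the escalation probabilities. They show why the figure matters and are not further errors in the protocol. The finding does not imply that 3 per cohort is too few for this phase I study, or that the hypothesis has to be rewritten.

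**What to change.** Amend the sentence in Section 9.1 to three cohorts of 3 subjects each, 9 in total, plus at most two replacements per cohort under Section 9.3. It then agrees with the Schema and Sections 3.0, 4.3 and 5.1.1, and the cohort size behind the escalation rule is the same throughout.

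The cost is one sentence in a protocol amendment. It adds no patients or procedures and changes no dose, escalation criterion or analysis.

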#### 9.1.1 Primary Objectives

To evaluate the safety and tolerability of three different doses of LC002 in HIV-infected patients on HAART.

#### 9.1.2 Secondary Objectives

To explore the immunogenicity of the LC002 for the treatment of individuals with chronic HIV-1 infection and who have HAART-induced durable suppression of viral replication.

#### 9.1.3 Dose Escalation Rule

Dose escalation will occur if

- 1) at least 2 subjects were on study until at least 14 days after receiving their study vaccination and
- 2) no subject in the current or lower dose cohort experienced a Primary Safety Endpoint.

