### 9.2 Endpoints

#### 9.2.1 Primary endpoint: Safety

Occurrence of at least one grade 3 or higher adverse event including signs/symptoms, lab toxicities and clinical events that is "possibly, probably," or "definitely" related to study treatment (as judged by the Principal Investigator, including site clinicians on the team) any time from the first day of study treatment until 28 days after LC002 administration.

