### 9.3 Accrual

Any subject who withdraws from the study prematurely without experiencing a primary safety endpoint before Week 4 evaluation, and whose reasons for withdrawing from the study are unrelated to any real or perceived effect of the study vaccination or its administration, will be replaced with a subject assigned to the same dose cohort and the same arm. If possible, all subjects who discontinue the study prematurely will be followed for 48 weeks for study treatment safety information. A maximum of two subjects per cohort will be replaced.

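### Section 9.1.3 escalates the dose on 2 subjects at Day 14, section 4.3 describes all 3, and no text reconciles them when one subject leaves early

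*Protocol*

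**What the plan says.** Four parts of the protocol bear on when the next dose cohort opens. Each cohort has 3 subjects (Schema, sample size).

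- **Section 9.1.3, Dose Escalation Rule.** Escalation follows if "at least 2 subjects were on study until at least 14 days after receiving their study vaccination" and "no subject in the current or lower dose cohort experienced a Primary Safety Endpoint".
- **Section 4.3, Study Enrollment Procedures.** The next cohort opens "After all 3 subjects of a given cohort (#1 or #2) have received their study vaccine administrations, and have remained on study" through at least Day 14, again provided that there is no Primary Safety Endpoint. The section cites 9.2.1 for the endpoint but does not cite 9.1.3.
- **Section 3.0, Study Design.** Later cohorts start only once safety data are available and "the criteria for enrolling into the next cohort are met (see section 9.1.3"). It does not mention 4.3.
- **Section 9.3, Accrual.** A subject who withdraws before the Week 4 evaluation without an endpoint, for reasons "unrelated to any real or perceived effect of the study vaccination or its administration, will be replaced", up to two per cohort. Other early leavers are not replaced. It adds: "If possible, all subjects who discontinue the study prematurely will be followed for 48 weeks for study treatment safety information". It does not say whether escalation waits for a replacement.

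**The concern.** The two escalation statements concern the same decision, the same day and the same blocking event, but one counts 2 subjects and the other counts 3. Escalation is the only decision rule in the trial, and it is applied twice: from 0.1 to 0.4 mg DNA, then from 0.4 to 0.8 mg. If one subject leaves early, staff working from 9.1.3 would open the next dose while staff working from 4.3 would wait. The protocol itself plans for such withdrawals in 9.3.

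**Working it through.** **1. Apply both rules to every possible headcount.** Assume that no Primary Safety Endpoint has occurred and count the subjects on study at Day 14 in a cohort of 3, before any replacement.

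| On study at Day 14 | 9.1.3 (at least 2) | 4.3 (all 3) |
|---|---|---|
| 0 | condition not met | condition not met |
| 1 | condition not met | condition not met |
| 2 | escalate | condition not met |
| 3 | escalate | escalate |

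The rules part only in the row with 2, that is, when exactly one of three leaves before Day 14. A withdrawal between Day 14 and Week 4 leaves both satisfied.

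**2. Add the replacement rule in 9.3 to that row.**

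- *Withdrawal unrelated to the vaccine.* The subject is replaced. 9.1.3 is already met by the two who remain; 4.3 is met once the replacement reaches Day 14. The difference is a delay of at least 14 days.
- *Withdrawal due to a real or perceived vaccine effect, without a Primary Safety Endpoint.* There is no replacement. 9.1.3 is met; the condition in 4.3 can never be met.

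**3. Check the blocking event.** 9.1.3 looks at the current and lower cohorts, 4.3 at any cohort. At the time of the decision no higher cohort has opened, so these coincide. A related grade 3 or higher event in the leaver blocks escalation under both sections.

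**4. Size.** The protocol gives no operating characteristic for the rule, so there is no stated figure to reproduce. With zero events in n fully observed subjects, the one-sided 95% upper bound on the risk is 1 − 0.05^(1/n):

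- n = 3: 1 − 0.05^(1/3) = 0.632
- n = 2: 1 − 0.05^(1/2) = 0.776

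These bounds apply to risk over the 14 days before the decision. The endpoint in 9.2.1 has a longer window, "any time from the first day of study treatment until 28 days after LC002 administration". The value for n = 2 is the limiting case in which the leaver contributes nothing.

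The same contrast can be shown as the chance of seeing no event, (1 − p)^n, at assumed 14-day risks p (the documents give none):

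| Assumed p | n = 3 | n = 2 | Difference |
|---|---|---|---|
| 0.10 | 0.729 | 0.810 | 0.081 |
| 0.20 | 0.512 | 0.640 | 0.128 |
| 0.30 | 0.343 | 0.490 | 0.147 |
| 0.40 | 0.216 | 0.360 | 0.144 |

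**The case against.** The strongest answer is that the sections do not truly compete. Section 3.0 ties the opening of later cohorts to 9.1.3, whose title marks it as the rule. Section 4.3 is an enrollment procedure. It says what happens after all 3 reach Day 14 and never says that escalation may happen only then. On that view it describes the normal course with nobody leaving, and 9.1.3 sets the floor. Much of this stands: the cross-reference favours 2 as the minimum, and a ban on escalating with two subjects is an inference from 4.3, not its wording. But 4.3 gives a complete rule with its own count, mentions no exception, and is not made subordinate to 9.1.3 anywhere. If 2 suffices, its count of 3 does no work.

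A reader might also infer more than the documents support:

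- *That a vaccine-attributed departure short of an endpoint is left unanswered.* It is not. 9.1.3 answers that escalation goes ahead. The difficulty is that 4.3 does not agree.
- *That 9.1.3 ignores what happens to the leaver.* Its second condition covers every subject in the cohort, and 9.3 asks that leavers be followed where possible. The leaver drops out only of the Day-14 headcount.
- *That the conflict will arise often.* With a chance d of leaving before Day 14 without an endpoint, exactly one of three does so with probability 3d(1 − d)², which runs from 0.058 at d = 0.02 to 0.384 at d = 0.20. Those values of d are assumptions. Nothing in the protocol supports any of them, and the treatment is a single application with patches removed at the clinic after 3 hours.
- *That 63% against 78% compares the two rules for any one withdrawal.* It does so only if a replaced leaver gives no information. If the leaver gives half the 14-day window at constant hazard (an assumption), the comparison is n = 2.5 against n = 3.5, or 0.698 against 0.575. For a leaver who cannot be replaced, 4.3 is unmet and there is no comparator.

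**Conclusion.** The inconsistency is real but narrow. The sections agree whenever all three subjects reach Day 14, whenever fewer than two do, and whenever a Primary Safety Endpoint has occurred. They differ for one early leaver without an endpoint: in timing if the withdrawal is unrelated to the vaccine, and lastingly if it is attributed to the vaccine. The contradiction rests on the wording alone and needs no assumed rate. How often it would arise cannot be known from the documents. When it does, escalating on two subjects means accepting a 14-day upper bound of up to 78%, against 63% with three fully observed. It should be fixed because it touches the trial's only decision rule and is cheap to remove. It does not show that the trial would escalate past an observed dose-limiting event.

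**What to change.** State one rule in 9.1.3 and have 4.3 refer to it without a count of its own. Suggested wording:

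> Dose escalation will occur only if (1) 3 subjects of the current cohort, counting any replacement under 9.3, have completed 14 days on study after vaccination, except as stated below, and (2) no Primary Safety Endpoint has occurred in that cohort or any lower one. Exception: if 3 such subjects cannot be reached because a leaver is not replaceable under 9.3 or both replacements have been used, and at least 2 subjects have completed 14 days with condition (2) met, escalation is held until the Principal Investigator and the sponsor have reviewed the safety data, including the leaver's, and documented the decision.

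Section 9.3 and its limit of two replacements stay as they are. Making 4.3 defer to the present 9.1.3 would also remove the contradiction, but escalation would remain automatic on two subjects after a vaccine-attributed departure. The count of 3 is already in the protocol and is the safer choice.

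The cost is amendment wording and, only if a subject leaves early, either a delay of at least 14 days for the replacement or one documented review.

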### 6.2.2 On-Study Evaluations

#### Entry

Evaluations should occur after enrollment prior to vaccine administration and at least 24 hours after the pre-entry evaluations.

All subjects will visit the clinic on the weeks  $\pm$  3 days indicated in the Schedule of Events. Vaccine administration has to occur on the weeks indicated in the Schedule of Events  $\pm$  0 days.

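### Sections 9.1.3 and 4.3 let dose escalation proceed on days on study rather than completed safety evaluations, and Section 3.0 does not say which safety data must be available

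*Protocol*

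**What the plan says.** **Data availability.** The Schema states that enrollment into the medium- and high-dose cohorts "will begin only after the safety data for cohort 1 and 2, respectively, are available" and the criteria for the next cohort are met. Section 3.0 repeats this: enrollment begins "only after the safety data for cohorts 1 and 2, respectively, are available, and the criteria for enrolling into the next cohort are met", with a pointer to Section 9.1.3. Neither place says which data are meant, or through which study day.

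**Escalation criteria.** Section 9.1.3 provides for escalation on two conditions: "at least 2 subjects were on study until at least 14 days after receiving their study vaccination" and "no subject in the current or lower dose cohort experienced a Primary Safety Endpoint". Section 4.3 gives its own version. All three subjects must have been vaccinated and must "have remained on study through at least the 14th day", with no Primary Safety Endpoint in any cohort; the next cohort then opens.

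**Evaluations.** Sections 6.0 and 6.1 schedule the targeted examination, vaccine-site evaluation, hematology, chemistries, liver tests and urinalysis on Days 0, 7, 14 and 28. Section 6.2.2 says "All subjects will visit the clinic on the weeks" given in the schedule, with a tolerance of 3 days either side.

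**Endpoint.** Under Section 9.2.1 the Primary Safety Endpoint is a Grade 3 or higher event at least possibly related to treatment. It includes laboratory toxicities and runs to 28 days after administration.

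**The concern.** The availability condition appears in the descriptive sections and is absent from the two places where the criteria are set out. Staff applying Section 9.1.3 or 4.3 as written would check a calendar and a list of reported endpoints. They would not check whether the Day 14 tests had been done.

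An endpoint with a laboratory component cannot be scored from a sample not yet drawn. A subject whose Day 14 tests are outstanding has no recorded endpoint from them and so passes the second condition by default. The error runs one way: missing information can only make the cohort look cleaner. With three subjects per cohort and a rule that turns on a single event, one unseen event is enough to reverse the decision.

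**Working it through.** The protocol gives no operating characteristic for the escalation rule, so there is no figure of its own to reproduce. The check is a comparison of texts, then calendar arithmetic, then an illustration.

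**1. Texts side by side**

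| Place | Follow-up condition | Requires data or evaluations? |
|---|---|---|
| Schema, 3.0 | Refers to the criteria (3.0 cites 9.1.3) | Yes, but no content or cut-off day |
| 9.1.3 | At least 2 subjects, 14 days on study | No |
| 4.3 | All 3 subjects, through Day 14 | No |

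Both 9.1.3 and 4.3 are phrased as sufficient: if the conditions hold, escalation follows. They also differ from each other on the number of subjects.

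**2. Calendar**

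I take the 3-day tolerance in 6.2.2 to apply to the Day 7 and Day 14 visits.

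- Day 14 visit: 14 − 3 = Day 11 to 14 + 3 = Day 17.
- Day 7 visit: 7 − 3 = Day 4 to 7 + 3 = Day 10.
- The day count can be met on Day 14, which is up to 17 − 14 = 3 days before an in-window Day 14 visit.
- If the Day 7 visit was kept in its window, the latest scheduled data at that moment are between 14 − 10 = 4 and 14 − 4 = 10 days old.

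**3. How often a counted visit would be outstanding**

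Assumptions, none from the protocol: visit days are uniform over Days 11 to 17, every visit is kept, consecutive vaccinations are g days apart, and the count is judged at the end of the last counted subject's Day 14. Laboratory turnaround is ignored.

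For subject i of n, the study day at that moment is d = 14 + g(n − i). The chance that the visit is done is min(d − 10, 7)/7, which is 4/7 at d = 14. Then P(at least one outstanding) = 1 − the product of these chances, and P(none done) = the product of their complements.

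| Gap g | At least one outstanding, n = 2 | n = 3 | None done, n = 2 | n = 3 |
|---|---|---|---|---|
| 0 days | 67.3% | 81.3% | 18.4% | 7.9% |
| 1 day | 59.2% | 65.0% | 12.2% | 1.7% |
| 2 days | 51.0% | 51.0% | 6.1% | 0% |
| 3 days or more | 42.9% | 42.9% | 0% | 0% |

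For example, with n = 3 and g = 0: 1 − (4/7)³ = 1 − 64/343 = 81.3%, and (3/7)³ = 27/343 = 7.9%. Results still pending would add to the outstanding share.

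**4. Direction of the effect**

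Let p be the true 28-day endpoint rate and f the share of endpoints visible at the decision. The chance of seeing none is (1 − pf)ⁿ. With p = 0.3 and n = 3 this is 34% at f = 1, 47% at f = 0.75 and 61% at f = 0.5. With n = 2 it is 49%, 60% and 72%. Both p and f are assumed. A Day 14 decision leaves part of the 28-day window unseen even when every visit is complete, so these figures show direction only and not how much is due to this gap.

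**The case against.** The strongest reply is that the sections should be read together. Section 3.0 joins data availability to the 9.1.3 criteria with a plain conjunction and cites 9.1.3 for the second part only. On that reading 9.1.3 never displaces the first part, and there is no outright contradiction. This stands. It does not close the gap, because 3.0 leaves the data undefined: Day 7 results alone, or whatever exists on the day, would satisfy it.

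Second, 9.1.3 and 4.3 do more than count days. They also require no Primary Safety Endpoint, which Section 9.2.1 has the Principal Investigator judge. Sections 6.3.6 and 7.1.2 and the laboratory instructions set 48-hour limits for recording or notification. That is a real safeguard for symptoms and for results that exist. It cannot supply a laboratory result from a test not yet done.

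Three stronger readings are tempting, and the documents do not support them.

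- A reader might infer that the next dose can open before any Day 14 evaluation at all. That is permitted but narrow: in the table above it needs near-simultaneous vaccination and late attendance by every counted subject.
- A reader might argue from Section 8.0 that a subject who misses a single visit remains on study. Section 8.0 lists criteria for stopping treatment, which here is one application on Day 0. It does not define being on study.
- A reader might recompute an upper confidence bound with one subject fewer. A subject evaluated at the Day 7 visit is not unevaluated, and 9.1.3 already allows two subjects with every test complete, so that bound would not measure this gap.

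**Conclusion.** The point holds as a defect in how the rule is fixed: the stated escalation criteria can be met without the data on which the decision depends, and the section that asks for the data does not define them. The calendar result, up to 3 days, rests only on the protocol's own window. The 43% to 81% range also needs the visit-day and spacing assumptions and should be read as showing that an outstanding visit would be ordinary, not rare.

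The decision would not be blind. Day 7 evaluations would normally be in hand, and symptomatic events can surface between visits. The exposure is mainly to laboratory toxicities and examination findings that would first appear at the Day 14 visit. That is enough to warrant correction in a first dose-escalation step with three subjects per cohort, but it does not show that escalation would in practice have ignored available data. The choice of a 14-day decision against a 28-day endpoint is a separate matter and is not judged here.

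**What to change.** Reconcile the Schema and Sections 3.0, 4.3 and 9.1.3:

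- Carry the data-availability condition of Section 3.0 into 9.1.3 and 4.3, so that a subject counts towards escalation on scheduled safety evaluations performed and graded, and not on elapsed time alone.
- State in Section 3.0 which scheduled evaluations make up the safety data. That choice is the sponsor's.
- In the same edit, resolve the conflict between at least two subjects (9.1.3) and all three (4.3), so that one rule remains. Which number applies is likewise for the sponsor.

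The toxicity threshold and the dose steps are untouched. The cost is a short amendment to four places and possibly a slower escalation. If the evaluations chosen include those of Day 14, the wait beyond the present count is at most 17 − 14 = 3 days for an in-window visit, plus laboratory turnaround, which the protocol does not state.
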